### Analysis plan- secondary aim: mediation analysis

Mediation will be examined using the approach described by Baron and Kenny [42], and further extended by MacKinnon [43] and Brown [44]. We will determine the extent to which possible intervention effects on academic achievement (an a priori condition for mediation) might be explained by changes in cognitive function, BMI, cardiovascular fitness, attention-to-task, and daily physical activity.

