**Methods/design:**

Seventeen elementary schools were cluster randomized to A + PAAC or control for a 3-year trial. Classroom teachers were trained to deliver academic instruction through moderate-to-vigorous physical activity with a target of 100+ minutes of A + PAAC activities per week. The primary outcome measure is academic achievement measured by the Weschler Individual Achievement Test-III, which was administered at baseline (Fall 2011) and will be repeated in the spring of each year by assessors blinded to condition. Potential mediators of any association between A + PAAC and academic achievement will be examined on the same schedule and include changes in cognitive function, cardiovascular fitness, daily physical activity, BMI, and attention-to-task. An extensive process analysis will be conducted to document the fidelity of the intervention. School and student recruitment/randomization, teacher training, and baseline testing for A + PAAC have been completed. Nine schools were randomized to the intervention and 8 to control. A random sample of students in each school, stratified by gender and grade (A + PAAC = 370, Control = 317), was selected for outcome assessments from those who provided parental consent/child assent. Baseline data by intervention group are presented.

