To provide increased MVPA while maintaining academic instruction time, a program titled “Physical Activity Across the Curriculum” (PAAC) was developed in which elementary school classroom teachers were trained to deliver academic lessons using MVPA with a primary aim to prevent increased BMI [10,11]. The impact of PAAC (2–10 minute lessons/day, 5 days/week) on academic achievement was assessed as a secondary analysis in a 3-year cluster randomized trial (PAAC vs. control) at baseline and at the end of year 3 in a random sub-sample of students (n = 252), in grades 2 or 3 at baseline, using the Weschler Individual Achievement Test-Second Edition (WIAT-II) [12]. Significant improvements were shown for all academic measures in students attending PAAC, but not for students attending control schools. Based on the evidence from both the literature [1,2,6,13-16] and the PAAC study [10,11], a 3-year trial will be conducted to evaluate the impact of physically active instruction on academic achievement in elementary school students in grades 2 and 3 at baseline. A + PAAC will alter the classroom environment by providing existing academic lessons taught using physical activity. Thus, the amount of time devoted to academic instruction is not diminished. The primary aim of this study is to assess differences in academic achievement in students who receive physically active lessons and students in control schools who receive regular academic lessons. Secondary aims include determining potential mediators of any association between A + PAAC and academic achievement, including changes in changes in cognitive function, cardiovascular fitness, daily physical activity, BMI and attention-to-task. An extensive process analysis will also be performed to document the fidelity of the intervention. This article describes the rationale and design of this study and presents baseline characteristics of both the participating schools and the study sample. Other data collected at baseline is currently being analyzed and will be the focus of forthcoming manuscripts.

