### Outcome measures

#### Research staff training and blinding

All outcome measures were assessed at baseline (Fall 2011) and will be repeated each Spring over the 3 year intervention. Two groups of research staff were trained by members of the investigative team to obtain outcome and process assessments. One group was trained on the observations of physical activity in the classroom and attention-to-task, while the second group was trained on the assessment of academic achievement, cognitive function, daily physical activity, height/weight, and cardiovascular fitness. Prior to data collection and then at the beginning of each data collection period, research staff will participate in several training sessions to review and practice standardized protocols for all assessments. Inter-rater reliability of > 0.90 will be required of all research staff prior to participation in data collection. Research staff obtaining measures of physical activity and attention-to-task in the classroom cannot be blinded to intervention group. However, staff obtaining all other assessments and those performing data entry will be blinded to intervention group.

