## Results

### Analysis plan-primary aim: academic achievement

Changes (year 3 minus baseline) in academic achievement (WIAT-III comprehensive score) will be compared between students attending A + PAAC intervention and control schools using a modified two-sample *t*-test adjusted for the intra-class correlation (ICC) [41] with a type I error rate of 5%. Similar analysis will be completed for WIAT-III sub-scales and for each of the secondary endpoints (Kansas State Assessment, cognitive function, BMI, cardiovascular fitness, attention-to-task, daily physical activity). This longitudinal study will provide multiple assessments over time; therefore linear mixed models will be used to assess differences in between A + PAAC and control in the primary and secondary endpoints. A compound symmetric correlation structure for estimating the intraclass correlation coefficient (ICC) within a school is assumed.

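### The mediation plan makes an intervention effect on achievement a precondition; an indirect effect does not need one, and the secondary aim could go unanswered if the true effect is smaller than planned

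*Protocol article*

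**What the plan says.** The Background section makes mediation a named aim: "Secondary aims include determining potential mediators of any association between A + PAAC and academic achievement". The section on the secondary-aim analysis begins "Mediation will be examined using the approach described by" and cites a causal-steps source with two later extensions. The question it then sets is how far "possible intervention effects on academic achievement (an a priori condition for mediation) might be explained by changes in cognitive function, BMI, cardiovascular fitness", with attention-to-task and daily physical activity completing the list. The parenthesis is the only statement on when mediation is examined. It gives no p-value, effect size or other criterion for the condition.

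The section does not define the interval over which mediator change is taken. The nearest text is elsewhere:

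- The abstract says that potential mediators "will be examined on the same schedule and include changes in cognitive function, cardiovascular fitness, daily physical activity, BMI, and attention-to-task".
- The primary-aim analysis compares "Changes (year 3 minus baseline) in academic achievement" between arms and adds "Similar analysis will be completed for WIAT-III sub-scales and for each of the secondary endpoints".
- The section on staff training and blinding says "All outcome measures were assessed at baseline (Fall 2011) and will be repeated each Spring over the 3 year intervention".

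**The concern.** An indirect effect is the product of the arm-to-mediator path and the mediator-to-outcome path. Both can be present, and estimable, when the total effect is too small to reach significance. This happens when paths of opposite sign offset each other. It also happens when the total effect, being a product of two fractions, is small compared with either path. Requiring the total effect first therefore puts what may be the least powerful test ahead of the analysis.

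At stake is the secondary aim. If A + PAAC has a real but smaller effect than planned, the primary test may miss. The plan as worded would then not examine mediation, although that is when it is most useful to know whether fitness, cognition or activity moved and whether achievement moved with them.

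**Working it through.** **Inputs from the protocol article.** Nine and 8 schools (abstract and study design); 40 students recruited per school, SD 9 points, planned difference 5 points, anticipated ICC 0.03 to 0.07, type I error 5% (sample size section). The 687 students in Table 2 over 17 schools also give about 40 each.

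**Assumptions.** Two-sided test; the condition means significance of the primary comparison; no dropout; smaller true effects of 3, 2.5 and 2 points. None of these is stated in the document.

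**Step 1: reproduce the plan's own power.** With design effect DE = 1 + (m − 1) × ICC, SE = SD × √[DE/(k₁m) + DE/(k₂m)] and power = Φ(δ/SE − 1.96), the Table 3 row for 7 schools per arm and 30 students gives 0.986, 0.953, 0.905 and 0.822 at ICC 0.03, 0.05, 0.07 and 0.10. The table states 0.99, 0.95, 0.90 and 0.82. All 24 cells agree within 0.02. The method is sound for the next step.

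**Step 2: chance of meeting the condition in the trial as randomized.** Here k₁m = 9 × 40 = 360 and k₂m = 8 × 40 = 320, so SE = 9 × √[DE × (1/360 + 1/320)] = 0.691 × √DE. The first figure in each cell is from a noncentral t with 9 + 8 − 2 = 15 df. The second, in brackets, is from the normal formula of step 1.

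| | ICC 0.03 | ICC 0.05 | ICC 0.07 | ICC 0.10 |
|---|---|---|---|---|
| DE | 2.17 | 2.95 | 3.73 | 4.90 |
| SE (points) | 1.019 | 1.188 | 1.335 | 1.531 |
| 5 points (planned) | 0.996 (0.998) | 0.975 (0.988) | 0.938 (0.963) | 0.863 (0.904) |
| 3 points | 0.79 (0.84) | 0.66 (0.71) | 0.56 (0.61) | 0.45 (0.50) |
| 2.5 points | 0.63 (0.69) | 0.50 (0.56) | 0.42 (0.47) | 0.33 (0.37) |
| 2 points | 0.45 (0.50) | 0.35 (0.39) | 0.29 (0.32) | 0.23 (0.26) |

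At 2.5 points and ICC 0.03 to 0.07, the aim goes unanswered with probability 1 − 0.63 = 0.37 to 1 − 0.42 = 0.58 (normal formula: 0.31 to 0.53).

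**Step 3: would mediation have been detectable without the condition?** Step 2 is power for the primary comparison, not for mediation, so a simulation compared the two (4000 runs per scenario; school-mean t-test for arm effects, within-school regression for the mediator-to-outcome path). The arm-to-mediator effect was 0.5 SD, the size used in the plan's secondary power statement. The mediator-to-outcome coefficient was assumed to be 0.4, with all of the effect mediated. The total effect is then 0.5 × 0.4 = 0.20 SD, or 0.20 × 9 = 1.8 points.

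| | ICC 0.03 | ICC 0.05 | ICC 0.07 |
|---|---|---|---|
| Total effect significant | 37% | 28% | 26% |
| Both paths significant | 98% | 93% | 89% |
| Both paths significant, total not | 61% | 66% | 65% |

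With a coefficient of 0.5 (total 0.25 SD) the last row becomes 44%, 52% and 55%. In these scenarios the condition itself, and not a shortage of data on the paths, causes most of the loss. They are illustrations with assumed coefficients and full mediation, so they favour the path tests.

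**The case against.** **The condition may not be a significance gate.** The text speaks of possible effects and gives no cut-off, and the cited extensions, which cannot be seen here, may relax it. This stands as a limit on the numbers. It does not remove the point, because the sentence itself keeps an effect on achievement as a precondition.

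**The aim is worded conditionally.** The Background section speaks of mediators of any association, so with no association there is arguably nothing to explain. But a non-significant result is not evidence of no association, and a true effect of 2 to 3 points is an association that the test would often miss.

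**The condition rarely binds at the design effect.** This is correct: 0.938 or higher across the anticipated ICC range. The smaller effects are assumptions. They are not far-fetched, since the 5 points comes from a secondary analysis in a sub-sample of 252 students and the Background section calls the prospective evidence inconsistent.

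**A reader might also infer that mediator and outcome changes share one window, so that mediator and consequence cannot be told apart.** The document does not support that as a finding. The mediation section names no window. The year-3-minus-baseline wording governs comparisons between arms, and the same section adds "This longitudinal study will provide multiple assessments over time". A shared measurement schedule is what would permit lagging, and a condensed article may leave the model to a fuller plan. Attention-to-task follows the classroom observation schedule, with observation every other week, and not only the spring visits.

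**A reader might illustrate cancelling paths with lost lesson time.** The article says in the Background and Discussion sections that instruction time is not reduced, so that example should not be used. The general argument does not need it.

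**Conclusion.** The point holds for the precondition. The plan states it outright, and it is not needed for an indirect effect to exist or to be estimated. Read as 5% significance, it costs little at the planned 5 points. At half that effect it would leave the secondary aim unanswered in about 37% to 58% of trials for ICC 0.03 to 0.07. These figures rest on the two-sided significance reading, no dropout, 40 students per school and an effect size that the document does not give. The consequence is confined to a secondary, explanatory aim; the primary inference is untouched. Reverse causation from same-window changes is not established from the text and supports only an optional sensitivity analysis.

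**What to change.** Delete the parenthetical condition. State that, for each child-level mediator, the indirect effect (product of coefficients) will be reported with a 95% interval that respects school clustering, whatever the primary result, and labelled supportive. A multilevel model with arm at school level and mediator and outcome at child level, with a Monte Carlo or school-level bootstrap interval, would serve.

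As an optional sensitivity analysis, state the mediator window and relate an earlier-wave mediator (spring 2012 or 2013), adjusted for baseline mediator and baseline WIAT-III, to spring 2014 WIAT-III where the measure's schedule allows. Attention-to-task would need its own definition. Lagging helps with temporal order but does not remove mediator–outcome confounding, and it ignores mediator change after the chosen wave.

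The cost is a change of wording and modest programming, using follow-up that is already scheduled. The drawback is wide intervals with 17 schools.

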### Exploratory analysis

In addition to mediation analysis, baseline characteristics (BMI, gender, age, race, ethnicity as well as baseline levels of the secondary outcomes [see mediation analysis section]) will be evaluated as predictors of change in academic achievement. Each of these variables will be included in a linear mixed model, assuming a compound symmetric correlation within each school. Stepwise regression techniques will be used to determine the “best” predictor model. “Best” will be determined by minimizing the Bayesian Information Criteria among all the potential predictor equations.

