### Recruitment

The parents of students in grades 2 and 3 in both the A + PAAC and control schools received a brief flyer describing the study, including exclusion criteria and assessment procedures. Parents of students interested in participation returned a portion of the flyer providing their contact information to the school. The parents were then invited to attend an informal meeting at the school with both study staff and classroom teachers where the study was described. Descriptive characteristics of both the intervention and control schools are presented in Table 1.

**Table 1 T1:** Descriptive characteristics of schools participating in the study

	**Intervention**	**Control**
Total School Enrollment	369.7 ± 96.6	385 ± 121.9
Total 2^nd^ and 3^rd^ Grade Enrollment (N = 1902)	978	924
2^nd^ and 3^rd^ Grade Class Size	22.5 ± 5.3	20.4 ± 2.6
Urban/Rural Schools (n/n)	6/3	6/2
Minority (%)	23.8	30.2
Free/reduced lunches (%)	35.3	42.5

Values are N’s or mean ± standard deviation.

Students with physical or intellectual disabilities or learning disorders will receive A + PAAC or control as a function of attending a participating school; however, some students were ineligible to complete outcome assessments due to their disability (i.e. blind, severe intellectual disability, etc.). Baseline participant characteristics by intervention group are presented in Table 2.

**Table 2 T2:** A + PAAC: participant baseline characteristics

	**Intervention** **(n = 370)**	**Control** **(n = 317)**
Age (years)	7.6 ± 0.6	7.6 ± 0.6
Height (cm)	129.6 ± 6.5	129.6 ± 6.9
Weight (kg)	29.6 ± 7.2	29.6 ± 7.7
Waist (cm)	57.6 ± 7.5	57.1 ± 7.7
BMI Percentile	61.1 ± 29.3	61.1 ± 30.0
Female (%)	47.9	53.1
Minority (%)	16.3	23.2
Free/reduced lunches (%)	26.5	36.7

Values are mean ± standard deviation unless otherwise indicated.

*Note*. 698 students were randomized. 687 performed anthropometric testing.

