### Sample size/power

The primary aim of this study is to compare change in academic achievement (comprehensive score) between the two treatments (A + PAAC vs. control). Power calculations were based on results from a secondary analysis of change in academic achievement from the completed PAAC study [10,11]. Since this is a cluster randomized design or an inherent ICC within the schools was assumed. The primary analysis will be conducted using a modified two-sample *t*-test [41] using a type I error rate of 5%. Table 3 describes the power for a range of ICCs, number of schools per treatment, and sample sizes within each school assuming an expected improvement in academic achievement of 5 points in the A + PAAC group, no change in the control group with a common standard deviation of 9 points, similar to results from the PAAC study [10].

**Table 3 T3:** Statistical power

**Schools per treatment**	**Students per school**	**Intra-Class correlation**					
		**0**	**0.01**	**0.03**	**0.05**	**0.07**	**0.1**
6	20	0.99	0.98	0.93	0.87	0.8	0.71
6	30	0.99	0.99	0.97	0.92	0.86	0.76
7	20	0.99	0.99	0.96	0.91	0.86	0.78
7	30	0.99	0.99	0.99	0.95	0.9	0.82

An ICC in the range of 0.03 to 0.07 is anticipated for academic achievement, thus to ensure at least 85% power for this confirmatory study, 17 schools were randomized between the two treatment groups with 40 students being recruited per school. Based on the power analysis above, power will be sufficient with as few as 20 students per school and ICCs as high as 0.10. Given the limited preliminary data, exact power calculations are not possible for the secondary endpoints. However, assuming a type I error rate of 5%, secondary endpoints have the following power: 0.99, 0.99, 0.96, 0.91, 0.84 and 0.74, to detect an effect size of 0.5 standard deviations for ICCs equal to 0, 0.01, 0.03, 0.05, 0.07 and 0.10, respectively. Thus, the study will have sufficient power to detect any clinically meaningful difference on the secondary endpoints.

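### The exploratory predictor list includes race and ethnicity but not free/reduced-lunch status, and does not say that trial arm stays in the model, so a race coefficient may partly reflect income

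*Protocol article*

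**What the plan says.** The Exploratory analysis section names its candidates: "baseline characteristics (BMI, gender, age, race, ethnicity as well as baseline levels of the secondary outcomes [see mediation analysis section]) will be evaluated as predictors". The outcome is achievement change. The list has no open-ended marker such as a for-example. The model is then given: "Each of these variables will be included in a linear mixed model, assuming a compound symmetric correlation within each school". The search follows: "Stepwise regression techniques will be used to determine the “best” predictor model", with best defined as the smallest Bayesian Information Criterion (BIC) among the potential equations.

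Table 2, in the Recruitment section, describes the assessed children (370 intervention, 317 control). Two of its rows matter here: "Free/reduced lunches (%) 26.5 36.7" and "Minority (%) 16.3 23.2" (intervention first, control second). The lunch row shows the largest gap between arms among the table's percentage rows, and it is the table's only income-related variable.

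The Sample size/power section assumes an "expected improvement in academic achievement of 5 points in the A + PAAC group", no change in controls and a common SD of 9. The Missing data section names treatment among the factors to be examined. The Exploratory analysis section does not mention treatment, either as included or as excluded.

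**The concern.** Race and ethnicity are offered to the model search, and the income-related variable already held for these children is not. If children on free/reduced lunch gain less (or more) over three years, and if minority children are more often on free/reduced lunch, an equation that contains race but not lunch status credits part of the lunch difference to race. This follows from the candidate list, whatever search rule is applied to it.

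At stake is the reading of an exploratory result. A published equation that names race as a predictor of academic change is sensitive, and here it could not be separated from income even though the data to do so are in hand. The silence about arm is a smaller matter. Both arms are pooled and the trial expects arm to move the outcome, so readers should be told that arm is in the model.

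**Working it through.** The exploratory analysis states no figure of its own, so there is none to reproduce. The SD and effect used below are those of the power section. Table 3, which is built on them, reproduces to within 0.02 in all 24 cells with n per arm = k·m/(1 + (m - 1)·ICC).

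**Inputs from the protocol article.** n = 370 and 317. Minority 16.3% and 23.2%. Free/reduced lunch 26.5% and 36.7%. Arm effect 5 points, SD 9. ICC 0.03 to 0.07. Seventeen schools, with arm constant within a school.

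**Step 1: precision of the minority coefficient.**
- Minority children: 0.163 × 370 + 0.232 × 317 = 60.3 + 73.5, about 134. Others: 687 - 134 = 553.
- SE ≈ 9 × √(1/134 + 1/553) = 0.87, ignoring clustering. Simulations of the mixed model gave 0.8 to 0.9.

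**Step 2: the BIC threshold.**
- One extra term enters if |z| > √(ln 687) = 2.56. With no true effect and no bias, the chance is about 1%.

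**Step 3: lunch status omitted.**
- Shift in the minority coefficient = lunch effect on change × (lunch share in minority children - lunch share in others).
- Pooled shares are 31.2% for lunch and 19.5% for minority. The article gives neither the lunch-by-race cross-table nor a lunch effect on change, so both are **assumed**.
- If 31.2% of minority children are on free/reduced lunch, as in the whole sample, the gap is 0 and the shift is 0.
- If 50% are, the others' share is (0.312 - 0.195 × 0.50)/0.805 = 0.267 and the gap is 0.233. If 80% are, the others' share is 0.194 and the gap is 0.606.

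| Assumed deficit in gain, lunch children | Assumed gap in lunch share | Shift (points) |
|---|---|---|
| any | 0 | 0 |
| 2 | 0.233 to 0.606 | -0.47 to -1.21 |
| 2 to 4 | 0.30 to 0.50 | -0.6 to -2.0 |

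Together these give roughly -0.5 to -2 points. The extreme corner, 4 × 0.606 = 2.4, lies a little beyond that.

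The formula applies to the association within schools. A compound-symmetric school term takes up much of any between-school part, but not the within-school part. A simulation of the planned mixed model with assumed lunch effects of 2 to 3 points gave shifts of about -0.8 to -1.1, returning to about 0 once lunch status was added.

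**Step 4: chance that a null minority term passes the BIC threshold.**
- P(|Z + shift/SE| > 2.56) for a shift of 0.6 (0.69 SE) is about 3%. For a shift of 2.0 (2.30 SE) it is about 40%. The unbiased figure is about 1%.

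**Step 5: arm omitted.**
- Simulating 17 schools of 40 children with the 5-point arm effect, ICC 0.03 to 0.10 and no true minority effect, the mixed model without arm gave a mean minority coefficient of about -0.05 to -0.2 points. With arm included it was about 0 within simulation noise. The leak is at most 0.2/0.87 = 0.23 SE, so the selection chance stays near 1%.

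**The case against.** **Arm.** A reader might infer that leaving arm off the list loads the treatment effect onto race. From Table 2, 45.1% of minority children and 56.0% of the others are in the intervention arm, and 5 × (0.451 - 0.560) = -0.55 points. That figure belongs to a regression with no school term. The plan specifies a within-school correlation, and an omitted arm effect is purely a between-school difference, so the school term takes up most of it and Step 5 shows what remains. Nor does the article say that arm is excluded. The list is of baseline characteristics to be screened, and arm is not one. This objection stands. What is left is that the section should state that arm is in the model.

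**Lunch status.** A reader might also infer that race will carry an income effect. The documents do not support that. The outcome is change, so stable income differences in level cancel, and nothing in the article shows that lunch status affects gain or how strongly it is tied to minority status. This limits the claim to a conditional one.

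**Scope.** The analysis is exploratory, seeks prediction rather than cause, and appears in a condensed article. The prediction argument reduces what is at stake, although readers will still interpret a named predictor. The condensation argument is weaker: the article does not leave the candidates open, but lists them.

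**Conclusion.** The point holds in conditional form, as a minor improvement. The stated list offers race and ethnicity without free/reduced-lunch status, which is held for the assessed children and differs between arms by 36.7 - 26.5 = 10.2 percentage points. A race coefficient, or a selected equation that contains race, may therefore partly reflect income.

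The size cannot be derived from the documents. The range of roughly -0.5 to -2 points, and the rise in selection chance from about 1% to about 3–40% for shifts of 0.6 to 2.0 points, rest entirely on the assumed lunch effect and lunch-share gap. They also treat minority status as a single two-level term and take the gap to apply within schools. If lunch and minority status are unrelated, or lunch status does not affect gain, there is no shift.

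The missing statement about arm is a matter of clarity, not a material source of bias under the planned model. The primary comparison is not affected.

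**What to change.** In the Exploratory analysis section, add free/reduced-lunch status to the candidate predictors and keep it in any equation that contains race or ethnicity. State that trial arm is a fixed term in every candidate equation. Leave the rest of the section unchanged.

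The cost is a sentence or two. Arm is known through the school and lunch status is already reported for the sample in Table 2, so no new data are needed. The two terms use two degrees of freedom with about 687 children. Reporting the lunch-by-minority cross-table beside the selected equation would let readers see how far the two can be separated.
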